The Residents-based Basic Health Insurance Schemes (RBHIS), established since 2009, were designed to prioritize inpatient services, leaving outpatient costs for hypertension and diabetes not covered or partially covered in most areas of China [15, 16]. Since 2019, the Chinese central government began to issue a series of RBHIS policy guidelines focusing on reducing outpatient costs for urban and rural patients with hypertension and diabetes [17]. Following the national guideline, several local chronic disease reimbursement schemes have been simultaneously established in many Chinese cities [18, 19]. By the end of 2019, Nantong City in Jiangsu province initiated an RBHIS reimbursement policy reform and improved hypertension and diabetes outpatient cost coverage. Before the RBHIS reform, outpatient costs for hypertension or diabetes were reimbursed only 400 Ren Min Bi (RMB) in a financial year. The new policy covers outpatient medication costs up to 50% or 1600 RMB per person for patients with hypertension or diabetes and 2000 RMB per person for patients with both diseases annually (essentials of the policy can be found in Additional file 1) [20, 21]. The policy applies to all registered hypertension and diabetes patients upon visiting designated public healthcare institutions. In order to qualify these outpatient benefit packages, hypertension or diabetes patients who are previously diagnosed, recorded in the chronic disease management system (CDMS), and continuously taking anti-hypertensive or anti-diabetic medications for treatment can register for the policy through the village clinics, township health centers (THCs), or secondary hospitals, while new patients have to be diagnosed with hypertension or diabetes and registered for the policy through a secondary hospital or above.

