### Study site

This study is being conducted in Tongzhou District, which is a district with high NCDs burden. According to a health census report based on medical examination data of regional health records of 125,769 participants aged over 65, the overall prevalence of hypertension and type 2 diabetes were 53.8% and 12.1%, while the control rates were 41.0% and 47.0%, respectively in 2017 [35]. Despite rapid urbanization in the past decade, a large socioeconomic gap remains between rural and urban residents of the district. In 2019, the annual disposable income of rural residents was 25,846 RMB (about 4011 United States Dollars (USD)), less than half of that of urban residents in Tongzhou district [36].

Tongzhou transferred from a rural county to an urban district in 2009 with a large proportion of the residents remaining rural. Rural areas are consisted of 12 townships, with 205 villages under these townships [37]. Two townships were selected to take part in this study based on the selection criteria of having (i) a typical representation of the socioeconomic development of rural areas of Tongzhou District, (ii) with village clinics serving 400 NCDs patients or more per year; (iii) available village doctors who can be trained to implement the intervention, and (iv) support from local healthcare institutions and township leaders. Majority of the residents in these two townships are under rural *hukou* (Chinese household registration system).

The local healthcare infrastructure is consistent with the primary healthcare system of rural China, characterized by a hierarchical system of county hospitals, district health centers (DHCs), THCs, and village clinics [38]. DHCs are secondary-level hospitals responsible for diagnosing and treating NCDs patients. There is one village clinic in each village with 3 to 7 village doctors carrying out regular quarterly follow-up visits on NCDs patients under the NEPHS program, mainly including monitoring blood pressure and blood glucose, health education, and medication consultation.

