**Medication costs and compliance**		
Medication purchase location	Patients, VDs	The most common place to buy medication is village clinics, followed by DHCs, pharmacies, secondary hospital or above.
		Most patients living near urban areas purchase medications in pharmacies due to lower price and more types of medications available.
		Most patients living near rural areas purchase medications in village clinics for convenience and lower price for some types of medications.
		Unavailability of certain medication types in village clinics. (This actually reflects the low awareness of policy details among patients, since policy applies to all public healthcare institutions, which have a great many type of medications available).
Medication costs	Patients	Hypertensive patients spend 30 to 50 RMB per month on self-medication, which is a low financial burden.
		Diabetic patients spend 200 to 300 RMB per month on self-medication, which is a heavy financial burden, and mainly due to the usage of insulin.
	Officials	Most patients with diabetes are also diagnosed with hypertension, adding up to the financial burden of self-medication.
Medication compliance	VDs	All interviewed VDs reported cases of medication self-discontinuation, especially among young patients, and attribute the situations to forgetfulness and insufficient awareness of comorbidity threats.

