### Outcome measurements

The primary outcome of the trial is the policy registration rate of NCDs patients recorded in CDMS. Information of NCDs patients registered in the policy will be collected and matched with CDMS at baseline, 3-month, and 6-month follow-up. Policy registration rate will be calculated as the proportion of NCDs patients registered in the policy in CDMS. The effectiveness of the intervention program will be evaluated by the policy registration rate between the intervention and the control arm. Secondary outcomes include the following:Total number of policy registrations including those that are not recorded in the hospital information system, collected at baseline and 6-month follow-up;Total hypertension and diabetes medication costs during duration of follow-up, collected at 6-month follow-up;Frequency of village doctor visits during duration of follow-up, collected at 6-month follow-up;Blood pressure level, including systolic blood pressure and diastolic blood pressure, measured with blood pressure monitor, if available from electronic health records or government-funded annual physical examination records;Blood glucose level, measured by blood tests, if available.

Data collection will rely on existing real-world administrative data (mainly insurance claims data) to reduce cost and increase study feasibility.

After the end of the follow-up period, we will also collect qualitative data through in-depth individual interviews of about six village doctors, ten patients, and several government officials and policymakers. Such data will provide insight on intervention fidelity, differential effects from different intervention components, and other feedback. We will conduct post-trial assessments relying on data collection from real-world administrative data periodically, to evaluate the longer-term effects of the intervention program. We will attempt dissemination of effectiveness of the intervention program through various channels, including policy forums or other forms with local healthcare officials. The trial schedule of procedures from beginning to end is shown in Fig. 3 below.

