### Statistical power

At the time of the contextual research and pilot study, the policy registration rate in villages of both the intervention and control arms was less than 10%. With an estimated sample of 5250 patients drawn from 15 villages in each arm and an estimated ICC of 0.04, the study is designed to provide more than 90% power (with a two-sided alpha of 0.05) to detect a difference in policy registration rate of at least 8.5% between intervention and control clusters [55, 56].

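### The combined medication-cost outcome ignores diagnosis in its main model although diabetes costs about six times as much as hypertension: a loss of precision, not a bias

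*Protocol article*

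**What the plan says.** The Outcome measurements section makes cost a single total over both diseases: "Total hypertension and diabetes medication costs during duration of follow-up, collected at 6-month follow-up". Table 1, under medication costs, reports that "Hypertensive patients spend 30 to 50 RMB per month on self-medication" and that "Diabetic patients spend 200 to 300 RMB per month on self-medication". It adds that "Most patients with diabetes are also diagnosed with hypertension".

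The Randomization section stratifies villages by township and by nothing else. The Analysis plan condenses patient data to village level and limits the main adjustment to stratification and clustering. Two further steps are foreseen: an additional analysis adjusting for baseline covariates found to be substantially imbalanced, and stratified analysis of possible effect modifiers. Diagnosis is named in neither.

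The Statistical power section covers registration only: "With an estimated sample of 5250 patients drawn from 15 villages in each arm and an estimated ICC of 0.04". No power is claimed for cost.

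**The concern.** A village with more diabetes patients has a higher mean medicine cost whatever its arm. With 15 villages per arm and no control of diagnosis in the design or the main model, that variation goes into the error of the cost comparison. Reducing medication costs is a stated secondary objective. If the saving is modest, a real effect could be missed, or the estimate could be too imprecise to interpret. Yet the main source of the noise is a baseline variable that the chronic disease management system (CDMS) already holds.

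**Working it through.** **1. The plan's own power figure, for registration.** Reading 5250 as per arm gives 5250/15 = 350 patients per village. The design effect is 1 + 349 × 0.04 = 14.96, so the effective sample is 5250/14.96 = 351 per arm. For 10% against 18.5%, power is 0.898 (pooled variance) or 0.901 (unpooled). It is 0.947 for 7% against 15.5% and 0.974 for 5% against 13.5%. The stated figure is reproduced to within rounding; it says nothing about cost.

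**2. Cost ratio (Table 1).** Midpoints: 250/40 = 6.25. Extremes: 200/50 = 4 and 300/30 = 10.

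**3. Diabetes share (assumed).** The Study site section gives prevalences of 53.8% and 12.1% in people over 65. With no overlap the share is 12.1/(53.8 + 12.1) = 18.4%; with full overlap it is 12.1/53.8 = 22.5%.

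**4. Mean cost.** 40 + 210 × 0.184 = 78.6 RMB per month, or 40 + 210 × 0.225 = 87.2. Diabetes patients carry 0.184 × 250/78.6 = 58% to 0.225 × 250/87.2 = 64% of spending.

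**5. Size of the intervention effect.** This step assumes that cost means what the patient pays, that 50% is reimbursed, and that the extra registrants have the same diagnosis mix as everyone else. The saving is 0.085 × 0.5 × 78.6 = 3.3 RMB, or 0.085 × 0.5 × 87.2 = 3.7 RMB, per patient per month.

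**6. Equivalent imbalance.** One point of diabetes share moves mean cost by 0.01 × (250 − 40) = 2.1 RMB. Then 3.34/2.1 = 1.6 points and 3.71/2.1 = 1.8 points. Over shares of 12-30% and the full cost ranges the threshold runs from 1.0 to 2.7 points. If a diabetes patient with hypertension costs 290 and all patients have hypertension, mean cost is 40 + 250 × 0.225 = 96.2, the saving is 4.09 and the threshold is 4.09/2.5 = 1.6 points.

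**7. How likely is such an imbalance?** The SD of the arm difference in share is √[2s(1 − s)(1 + 349ρ)/5250], with s = 0.184 and ρ the ICC of diabetes status. The documents do not give ρ, so a range is shown. The power columns come from 4000 simulated trials of 15 against 15 village means, with a within-diagnosis coefficient of variation of 0.5 (assumed) and the 3.3 RMB saving.

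| ρ | Village SD (points) | SD of arm difference (points) | P(imbalance over 1.6 points) | Power, unadjusted | Power, adjusted for village share |
|---|---|---|---|---|---|
| 0 | 0 | 0.76 | 4% | not run | not run |
| 0.005 | 2.74 | 1.25 | 20% | 21% | 82% |
| 0.01 | 3.87 | 1.60 | 32% | 16% | 82% |
| 0.04 | 7.75 | 2.93 | 59% | 8% | 82% |

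With no intervention effect, the unadjusted analysis rejects in 4-5% of runs, so type I error holds. The 82% is optimistic. The adjusted estimate has an SD of about 1.1 RMB, which is what patient variation alone gives: √[2 × (0.816 × 20² + 0.184 × 125²)/5250] = 1.1. Any other village-level variation in cost would lower the adjusted power.

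**8. Larger effects.** At a 30-point registration difference the threshold is 5.6 points, and it is exceeded with probability at most 6%. Unadjusted power is 99%, 93% and 50% at ρ = 0.005, 0.01 and 0.04. At 50 points the threshold is 9.4 points and the probability about 0.1% or less.

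**The case against.** The strongest reply is that villages are randomised, so diagnosis mix is noise that a cluster-level analysis with robust standard errors carries correctly. That stands. A reader might infer that chance imbalance makes the cost result unreliable in both directions; the simulated type I error shows that it does not. The possible loss is power, on a secondary outcome for which no power is claimed.

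Second, 8.5 points is the smallest difference the trial is sized for, not the expected one. In the pilot village registrations rose from 17 to 148 in a week. At 350-400 patients that would be 131/400 to 131/350, or 33-37 points. This also carries weight, although the pilot village's size is not given and it had no control. Savings may also lag registration, since Table 1 notes that some registered patients do not know they can claim.

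Third, registrants may be disproportionately diabetes patients. If half were (illustrative), the saving would be 0.085 × 0.5 × 145 = 6.2 RMB and the threshold 6.2/2.1 = 2.9 points. And if the outcome is cost saved, as the Abstract words it, one point of mix moves it by only 2.1 × 0.5 × 0.10 to 2.1 × 0.5 × 0.185, about 0.1-0.2 RMB. The Outcome measurements section, however, defines a total cost.

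Fourth, the plan foresees adjustment for imbalanced covariates and stratified analyses, and naming variables is ordinary SAP content. This answers only part of the point. The article does state the main adjustment set, and diagnosis is not in it. A difference such as 18% against 20% would hardly be called substantial. Stratified analysis addresses effect modification, not precision.

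**Conclusion.** The point holds for cost, as a matter of efficiency. Near the 8.5-point design difference, a 1.6-1.8 point arm difference in diabetes share equals the whole expected saving, and the unadjusted analysis would have little power (8-21% over the range of village spread shown). The concern fades at registration differences of 30 points or more, unless villages differ widely in mix. The size rests on rough inputs: interview cost figures, prevalences in people over 65, an assumed between-village spread and an assumed within-diagnosis variation. The primary registration outcome and its power are untouched.

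A reader might also infer that glucose and blood pressure are averaged over all patients regardless of diagnosis, which would dilute any glucose effect. The document does not say so. Glucose is listed only as "Blood glucose level, measured by blood tests, if available"; the analysis population for both measures is left unspecified, and the sixfold ratio concerns cost alone.

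**What to change.** In the Analysis plan, prespecify for the cost outcome that the main model includes baseline diagnosis group from CDMS (hypertension only, diabetes only, both). If the model is fitted to data condensed to village level, use the village's baseline diabetes share instead. Fix the diagnosis from records dated before the intervention starts, so that the covariate cannot be affected by it. Report the arm difference in cost within each diagnosis group, and form the groups before the data are condensed.

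The cost is a few sentences, slightly more analysis work, and one or two model degrees of freedom with 30 clusters. CDMS already identifies hypertension and diabetes patients, so no new data collection is needed.

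### Medication costs and village doctor visits are given no pre-trial value, so the main models for these two secondary outcomes forgo a covariate that could sharpen them and show chance imbalance

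*Protocol article*

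**What the plan says.** The Outcome measurements section sets collection times outcome by outcome. The registration rate is "matched with CDMS at baseline, 3-month, and 6-month follow-up". The total number of registrations is "collected at baseline and 6-month follow-up". The next two secondary outcomes are worded differently: "Total hypertension and diabetes medication costs during duration of follow-up, collected at 6-month follow-up" and "Frequency of village doctor visits during duration of follow-up, collected at 6-month follow-up". Neither has a pre-trial window.

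On the source, the same section states: "Data collection will rely on existing real-world administrative data (mainly insurance claims data) to reduce cost and increase study feasibility". It gives no date range and does not say which records supply the visit counts.

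The Analysis plan estimates effects by GEE with robust variance. The main models adjust for stratification and clustering. Baseline covariates are tabulated by arm, and those found imbalanced enter an additional analysis. A prior cost or visit value is not named among them.

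Reducing medication costs is a stated secondary objective.

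**The concern.** Thirty villages are randomized, stratified only by township. Village means of cost and visits are likely to differ before the trial for lasting reasons, such as disease mix, where patients buy medicines and clinic staffing (3 to 7 village doctors, per the Study site section). Table 1 shows how strongly cost depends on disease for a single patient: "Diabetic patients spend 200 to 300 RMB per month on self-medication", against 30 to 50 RMB for hypertension.

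With 15 villages per arm, some of that variation will fall unevenly by chance. A pre-trial value of the same measure is usually the best single covariate for removing it, and the most direct way to see it. Within one list the plan takes a baseline for registrations but not for costs or visits. At stake are the precision of these two secondary comparisons and the ability to check them for chance imbalance.

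**Working it through.** **The plan's own figure.** The only power statement concerns the registration rate, so it does not bear on costs or visits. It reproduces closely. Reading 5250 as per arm gives 5250/15 = 350 patients per village, a design effect of 1 + 349 × 0.04 = 14.96 and an effective size of 5250/14.96 = 350.9 per arm. For 10% against 18.5% the power is 89.8%; for 7% against 15.5% it is 94.7%. No power or precision figure is given for costs or visits.

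**Inputs.** 15 villages per arm and ICC 0.04 (Statistical power). Main model adjusted for stratum (Analysis plan). The correlation r between a village's pre-trial and follow-up mean is not in the documents; I assume a range from 0.3 to 0.8.

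**Where the variance lies.** If the ICC of 0.04 carried over to costs (an assumption), the between-village share of the variance of a village mean would be 350 × 0.04/14.96 = 14/14.96 = 94%. If 5250 is the total, there are 175 patients per village and the share is 7/7.96 = 88%. A village-level covariate therefore acts on the component that matters.

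**Size of chance imbalance.** In units of the between-village SD, the standard error of the difference between arms in pre-trial means is √(2/15) = 0.37, with a 95% range of ±1.96 × 0.365 = ±0.72.

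**Gain from adjustment.** The residual variance is multiplied by 1 − r² and the interval width by √(1 − r²). Detectable differences are for 80% power, two-sided 5%, by noncentral t with 27 df unadjusted and 26 df adjusted. Without a pre-trial value the detectable difference is 1.06 SD.

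| r (assumed) | 1 − r² | Interval narrows by | Detectable difference (SD) | Power for an effect with 80% unadjusted | Villages needed without the covariate, 30/(1 − r²) |
|---|---|---|---|---|---|
| 0.3 | 0.91 | 5% | 1.01 | 83.5% | 33 |
| 0.5 | 0.75 | 13% | 0.92 | 89.8% | 40 |
| 0.8 | 0.36 | 40% | 0.64 | 99.7% | 83 |

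**Disease mix alone.** The midpoints in Table 1 differ by 250 − 40 = 210 RMB a month. If the diabetes share had a between-village SD of 5 points (assumed), the standard error of the arm difference in share would be 5 × 0.365 = 1.8 points, or about 4 RMB per patient-month. At an SD of 10 points it would be about 8 RMB.

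**The case against.** **The plan does have a baseline check.** The Analysis plan looks for imbalance and adjusts for it in an additional analysis. The CDMS is the register of these patients, so disease mix should be available from it. This stands: it would be wrong to infer that the two outcomes have no baseline control. What the check lacks in the text is the prior value of the outcome itself, and the adjustment stays outside the main model.

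**Pre-trial records are not promised.** A reader might infer that the claims already hold the baseline. The protocol does not say so. It is likely for costs, because the data are existing claims and the Background reports that before the reform "outpatient costs for hypertension or diabetes were reimbursed only 400 Ren Min Bi (RMB) in a financial year". It is less sure for visits: nothing shows that routine quarterly follow-up visits generate claims.

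**The correlation may be low.** Table 1 reports substantial pharmacy purchasing, and the program aims to move purchases into designated institutions, so claims before and after may track each other poorly. That is why the table starts at r = 0.3, where the gain is small. Adjusting for disease mix as well would shrink it further.

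**Patient costs are not village costs.** A several-fold difference between diseases does not show several-fold differences between villages. The figures come from interviews in four villages, and the disease-mix sum above gives only a few RMB.

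**Bias.** A reader might infer that the cost comparison is biased. It is not. If a baseline imbalance of two standard errors occurred, the unadjusted test would err about 13% of the time at r = 0.5, but that is conditional on an unlucky draw. Averaged over randomizations the error rate is unaffected.

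**What is not shown.** Fig. 3 or the full protocol may list a baseline extract. The text sets none.

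**Conclusion.** The point holds as one of efficiency and checking. As written, costs and visits are collected for follow-up only, unlike the registration outcomes, and the main models carry no prior value of either. The randomized comparison stays valid, and the primary outcome is untouched.

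The forgone gain runs from modest (interval about 5% narrower at r = 0.3) through useful (13% at r = 0.5) to large (40% at r = 0.8). It rests on an assumed r and on administrative records reaching back before the trial. The documents support neither a claim that the baseline certainly exists nor a claim of systematic bias.

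**What to change.** Where the records cover the period, extract the same cost and visit measures for a pre-baseline window equal in length to follow-up (6 months). Use the same calendar dates in all 30 villages and the patients on the baseline CDMS list in both arms. State which records supply visits.

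Prespecify the pre-period value, at village or patient level, as a covariate in the main GEE for these two outcomes, before any comparison by arm is seen, and report it by arm. Keep the planned imbalance check for other covariates. If the schedule figure or full protocol already includes such an extract, align the Outcome measurements text with it.

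The cost is a wider date range in an extract already planned, and one covariate (one degree of freedom in the village-level calculation above). If pharmacy purchases or non-claimed visits are missing from the pre-period, the gain is smaller, but the adjustment does not bias the randomized comparison.
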